## 15.5 Efficacy analysis

### 15.5.1 Primary endpoints

Incidence of bacteremia within 1 month after living donor liver transplantation  
[Main analysis]

The incidence of bacteremia within 1 month after living donor liver transplantation and its 95% confidence interval will be calculated for FAS. In addition, the following statistical hypothesis test will be performed at a significance level of 5% (two-tailed) by chi-square test using the 30% incidence of bacteremia with non-NK therapy observed in previous studies as a threshold.

The null hypothesis: "The incidence of bacteremia  $p$  in NK therapy is equal to a threshold of 30% ( $p = 0.3$ )."

Counter-hypothesis: "The incidence of bacteremia  $p$  in NK therapy is less than the threshold of 30% ( $p < 0.3$ )"

### 15.5.2 Secondary endpoints

#### ① Overall survival time

FAS will be observed from the date of surgery to the date of death (regardless of the cause of death) or the date of confirmed survival, and the survival curve for overall survival will be estimated using the Kaplan-Meier method, and the median overall survival and its 95% confidence interval will be calculated. The median overall survival and its 95% confidence interval will be calculated. The survival rates at 6 months, 1 year and 3 years and its 95% confidence interval will be calculated. The Greenwood method will be used to calculate the confidence intervals.

- ② Effect on immune response (evaluation of donor-specific immune responsiveness by CFSE-MLR, detection of DSA, incidence of rejection, evaluation of NK cell activity in recipient peripheral blood).  
For CFSE-MLR and evaluation of recipient peripheral blood NK cell activity for FAS, summary statistics and changes from baseline (mean (median), standard deviation (quartiles)) and their 95% confidence intervals will be calculated for each observation time point. For detection of DSA and incidence of rejection, the number of cases in each category and its percentage will be calculated.
- ③ Hepatocellular carcinoma recurrence / De novo carcinogenesis  
We will observe whether hepatocellular carcinoma (HCC) recurs in FAS and the date of recurrence, and calculate the HCC recurrence rate and its 95% confidence interval, and the mean time to recurrence and its 95% confidence interval. De novo carcinogenesis will be analyzed in the same way.
- ④ Incidence of infectious diseases  
The percentage of subjects who developed bacterial, cytomegalovirus, and fungal infections and their 95% confidence intervals will be calculated. The incidence of infectious diseases by genetic polymorphism will be calculated, and comparisons between genetic polymorphisms will be made using Fisher's direct probability method at a significance level of 5% (two-sided).

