| Evaluation Items  | 
Primary endpoints
 
Incidence of bacteremia during the first month after surgery
 
Secondary endpoints
 
 
① Overall survival (6 months, 1, and 3 years postoperatively)
 
② Effect on immune response 
 
Evaluation of donor-specific immune responsiveness by CFSE-MLR (1, 2, 3, and 4 weeks postoperatively)
 
Detection of DSA (donor specific antibody) (annual screening)
 
Incidence of rejection
 
Evaluation of NK cell activity in peripheral blood of recipients
 
 
 
③ Presence of hepatocellular carcinoma recurrence (hepatocellular carcinoma cases only) 
 
Presence and timing of de novo carcinogenesis
 
 
 
④ Incidence of infectious diseases (bacterial infections, cytomegalovirus infections, fungal infections, analysis by
 
 |

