### 8.2 Secondary endpoints

① Overall survival (6 months, 1, and 3 years postoperatively)

② adverse event

Type and severity of adverse events that occurred in this clinical study, frequency of occurrence, duration of occurrence, and causal relationship

③ Effect on immune response

Evaluation of donor specific immunoreactivity by CFSE-MLR (1, 2, 3, 4 weeks postoperatively), detection of donor specific antibody (DSA) (annual screening), incidence of rejection, evaluation of NK cell activity in recipient peripheral blood

- ④ Presence and timing of hepatocellular carcinoma recurrence (hepatocellular carcinoma cases only) and De novo carcinogenesis
- ⑤ Incidence of infectious diseases (bacterial infections, cytomegalovirus infections, fungal infections, analysis by genetic polymorphism)

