### 15.2 Definition of the population for analysis

#### 15.2.1 Efficacy analysis population

Subjects who are enrolled in this clinical study and underwent living partial liver transplantation and NK cells were administered on postoperative day 3 will be the target population for efficacy analysis (the largest analysis set Full Analysis Set: FAS).

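### HCC recurrence is defined for carcinoma cases only but analysed in the FAS, and its timing is summarised by a mean that hardly responds to the recurrence risk

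*Protocol*

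**What the plan says.** Section 8.2 defines the endpoint as "Presence and timing of hepatocellular carcinoma recurrence (hepatocellular carcinoma cases only) and De novo carcinogenesis". The Overview carries the same limit: "Presence of hepatocellular carcinoma recurrence (hepatocellular carcinoma cases only").

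The analysis text in 15.5.2 (3) reads "We will observe whether hepatocellular carcinoma (HCC) recurs in FAS and the date of recurrence, and calculate the HCC recurrence rate", with a confidence interval, "and the mean time to recurrence and its 95% confidence interval". It ends: "De novo carcinogenesis will be analyzed in the same way".

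The FAS (15.2.1) is "Subjects who are enrolled in this clinical study and underwent living partial liver transplantation and NK cells were administered on postoperative day 3". Carcinoma is not part of that definition. Recipient eligibility (3.2) requires decompensated cirrhosis, not carcinoma. Section 7.4.6 ends observation 3 years after surgery.

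For overall survival, item (1) of the same section states that "the survival curve for overall survival will be estimated using the Kaplan-Meier method", with Greenwood intervals and survival rates at fixed times.

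**The concern.** There are two separate problems.

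**Population.** Recurrence can be assessed only in patients who had a carcinoma. De novo cancer can arise in any recipient, and 8.2 does not restrict it. The analysis section names one population, the FAS, for both. Read literally, the recurrence rate has too large a denominator. Read as carcinoma cases within the FAS, the instruction to treat de novo cancer identically would confine that endpoint to carcinoma patients. Neither reading suits both endpoints.

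**Time summary.** A mean time to recurrence is fixed without saying what happens to patients who die or reach 3 years without recurrence. The missing-value rules in 15.3 are framed around the robustness of the primary endpoint and give no rule for a censored recurrence date. An ordinary mean can use only patients who recur, and each of their times is at most 36 months.

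At stake is the readability of an endpoint that 8.2 includes to judge the effect of treatment on carcinogenesis. The rate could look low because of its denominator, and the mean could be taken for an effect measure that it is not.

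**Working it through.** The protocol gives no figure for recurrence or time to recurrence in this trial, so there is nothing of its own to reproduce. The nearest figure is the 5-year relapse-free survival of 74.5% in the 24 earlier recipients, all with carcinoma (2.2.3).

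**1. Denominator.** Let f be the carcinoma share of the FAS (not in the protocol; assumed 30 to 70%). Then

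rate on the whole FAS = f × rate in carcinoma cases,

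so the understatement factor is 1/f: 1/0.3 = 3.3 and 1/0.7 = 1.4. As an illustration, take an FAS of 34 (the calculated sample size in 7.2) and an assumed 3 recurrences, with Clopper-Pearson intervals:

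| Carcinoma share | Carcinoma cases as denominator | Whole FAS as denominator |
|---|---|---|
| 30% | 3/10 = 30.0% (6.7 to 65.2%) | 3/34 = 8.8% (1.9 to 23.7%) |
| 50% | 3/17 = 17.6% (3.8 to 43.4%) | 8.8% |
| 70% | 3/24 = 12.5% (2.7 to 32.4%) | 8.8% |

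**2. Mean time among those who recur, constant hazard.** With T = 36 months, 3-year risk R and λ = −ln(1 − R)/T,

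mean = 1/λ − T·exp(−λT)/(1 − exp(−λT)).

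| 3-year risk | 5% | 10% | 20% | 30% | 40% | 50% | 80% | 90% |
|---|---|---|---|---|---|---|---|---|
| Mean, months | 17.9 | 17.7 | 17.3 | 16.9 | 16.5 | 15.9 | 13.4 | 11.6 |

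A tenfold change in risk, from 5% to 50%, moves the mean by 17.9 − 15.9 = 2.0 months.

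Taking the earlier 74.5% as a constant hazard: λ = −ln(0.745)/5 = 0.0589 per year. The 3-year risk is 1 − exp(−3 × 0.0589) = 16.2% and the mean among observed recurrers is 17.5 months. The untruncated mean, 1/λ, is about 204 months.

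**3. Other hazard shapes.** Weibull hazards, 3-year risk rising from 10% to 50%:

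| Shape | Mean, months |
|---|---|
| 0.5 | 11.7 falling to 10.0 |
| 0.7 | 14.5 falling to 12.7 |
| 1.5 | 21.3 falling to 19.7 |
| 2 | 23.8 falling to 22.3 |

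At each shape the mean moves by less than 2 months across this range of risk. Its level depends on the shape, from about 10 to 24 months.

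**4. Is there an interval at all?** With an FAS of 34, a 16.2% risk and carcinoma shares of 30, 50 and 70%, the expected recurrences are 10 × 0.162 = 1.6, 17 × 0.162 = 2.8 and 24 × 0.162 = 3.9. The binomial probability of 0 or 1 recurrence, when a mean has no confidence interval, is 50%, 21% and 8%.

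**5. A summary that uses censored patients does respond.** The 36-month restricted mean recurrence-free time, constant hazard, is 34.2, 32.3, 30.3, 26.0 and 17.9 months at 3-year risks of 10, 20, 30, 50 and 80%.

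**The case against.** The best defence is that the sections can be read together. The limit to carcinoma cases stands in the Overview and in 8.2. Sections 9.2.1, 9.2.2 and 9.2.4 collect carcinoma history, diagnosis and Milan status only in those patients. On that reading the FAS is simply the set from which carcinoma cases are drawn. This stands as far as it goes: dilution is one reading, not a stated rule, and its size rests on a share that the protocol does not give. It does not settle the de novo sentence.

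Several stronger inferences are tempting and not supported:

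- *The mean is fixed near 17 months whatever the risk.* That needs a constant hazard and a moderate risk. The mean falls to 13.4 and 11.6 months at 80% and 90% risk, and hazard shape shifts it further. It also carries some information on early against late recurrence, which is part of the endpoint.
- *The rate is a crude proportion.* The text names no estimator. Item (1) uses the word rate for Kaplan-Meier estimates, and an unnamed estimator may be left to the SAP.
- *The mean must be over recurrers only.* A restricted mean would use everyone. The text does not say which is meant.
- *De novo cancer has the wrong population.* The full FAS suits it; only its mean time is at fault.
- *The recurrence rate will be compared with the earlier series.* 15.5.2 plans estimation only.

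The 74.5% is relapse-free survival and may count deaths, so the 17.5 months is an illustration. The conclusion rests on the range of risks instead.

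**Conclusion.** The point holds in a limited form. The endpoint definition and the analysis text disagree on population, and one population is given for two endpoints that need different ones. If the whole FAS is used for recurrence, the rate is understated by the inverse of the carcinoma share: 3.3- to 1.4-fold at an assumed 30 to 70%.

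The mean time is a statistic that the protocol itself fixes, not a detail left open. Taken as an ordinary mean over patients recurring within 3 years, it is largely insensitive to risk: about 16 to 18 months for 3-year risks of 5 to 50% under a constant hazard, with the level ranging from about 10 to 24 months across the hazard shapes tried. It may have no interval at all. The endpoint is secondary and descriptive, so nothing here touches the bacteremia test or the sample size. It should be corrected, but it does not threaten the trial's main conclusion.

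**What to change.** In 15.5.2 (3):

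- Name FAS patients with hepatocellular carcinoma as the denominator for recurrence, and the full FAS for de novo cancer.
- For both endpoints, replace the mean time with 1- and 3-year estimates and 95% confidence intervals that account for censoring. Either cumulative incidence with death as a competing event, or Kaplan-Meier recurrence-free survival (for de novo cancer, cancer-free survival), would do; the latter matches the method already chosen for overall survival. State which, because the two treat death differently.
- If a single time summary is still wanted, a restricted mean to 36 months is defensible.

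The cost is a few lines of analysis text and a standard procedure. Recurrence and death dates are already to be recorded under 15.5.2, and handling de novo cancer identically implies its dates too, so no new data are needed.

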## 15.6 Safety analysis

### *adverse event*

The number of cases, number of incidences, and percentage of incidences of adverse events will be tabulated by event and by severity. The number of cases, number of incidences, and percentage of incidences of adverse events by event type and severity will also be tabulated.

### *vital signs*

Summary statistics of the vital signs are obtained for the change at each time point from the observed values at the scheduled postoperative measurement time points and the observed values at the preoperative examination (baseline) and are listed in the table.

### *clinical laboratory test results*

Summary statistics of the clinical laboratory data (hematological and biochemical tests) will be obtained and listed for the amount of change at each time point from the observed values at the scheduled postoperative measurement time points and the observed values at the preoperative examination (baseline). For qualitative clinical laboratory data, the frequency of pairs of laboratory category values at baseline and each measurement time point is tabulated in the form of a contingency table.

## 15.7 Procedure for changing the analysis plan

If changes or additions to the analysis plan occur after the start of the study, the appropriateness of the changes or additions and their impact on the evaluation of the study should be considered, and the circumstances leading to the changes or additions to the analysis plan should be described in the summary report. For major analyses and analyses of important endpoints, changes to the protocol should be made as well.

## 16 Quality control for clinical research

### 16.1 Quality Control

Principal investigators, subcontractors, and research collaborators will conduct clinical research in compliance with the Act on Securing the Safety of Regenerative Medicine, etc., the Ethical Guidelines for Medical Research Involving Human Subjects, and this protocol. In addition, Principal Investigators, Research Associates, and Research Collaborators will conduct clinical research in accordance with their respective procedures for conducting clinical research.

### 16.2 monitoring

Since this clinical research falls under the category of research that involves invasion and intervention, the principal investigator will entrust monitoring to the Hiroshima University Hospital Center for Comprehensive Medical Care and Research, and will conduct monitoring in accordance with the standard procedures for quality control of clinical research owned by the center.

The person in charge of monitoring will conduct monitoring at a separately designated time to confirm that the research is being conducted appropriately in compliance with the Act on Securing the Safety of Regenerative Medicine, etc., the

Ethical Guidelines for Medical Research Involving Human Subjects, and this protocol, and that the reliability of the data is sufficiently secured. The results of the monitoring shall be reported to the principal investigator.

### 16.3 data management

The principal investigator or sub-investigator should describe and prepare the data obtained from the subject in the case report form without delay. The case report form, the donor liver-derived activated lymphocyte production instruction form, the consent form, and a copy of the test results will be filed for each case and stored in a locked archive in the Department of Gastroenterology and Transplantation, Hiroshima University Graduate School of Medicine. The prepared case report form will be submitted to the Data Center without delay, and the Data Center will manage the data in accordance with the Standard Procedure for Quality Control of Clinical Research owned by the Hiroshima University Hospital Center for Comprehensive Medical Care Research.

### 16.4 Effectiveness and Safety Evaluation Committee

#### 16.4.1 Details of deliberations by the Effectiveness and Safety Evaluation Committee

The Efficacy and Safety Evaluation Committee shall consist of three physicians, excluding the subcontractors, and shall deliberate on the following matters

- Contents of the annual implementation status report
- Confirmation of the efficacy and safety of the NK cells and whether the study should be continued at an interim total to be conducted at the end of the observation period of one month after the 15th surgery in which NK cells were administered.
- Assessment of serious adverse events
- Other matters as deemed necessary by the principal investigator or the Efficacy and Safety Evaluation Committee.

#### 16.4.2 Recommendations by the Effectiveness and Safety Evaluation Committee

When items to be recommended are proposed by the Effectiveness and Safety Evaluation Committee, the contents and reasons will be recommended to the principal investigator.

### 16.4.3 Audit

No audit will be conducted in this study.

## 16.5 Education and training of researchers

The principal investigators will provide education and training opportunities for researchers participating in this research before the start of the research and at least once per year after the start of the research to deepen their understanding of the following examples.

1. Ministry of Health, Labour and Welfare, "Act on Securing the Safety of Regenerative Medicine, etc.
2. Knowledge about specified cell processing products, etc. (including ethical concepts)
3. Knowledge and skills related to the safe handling of prepared processed cell culture products, etc.
4. Knowledge and skills related to facilities and equipment
5. Knowledge and skills related to the safety of the preparation process
6. Knowledge and skills regarding measures to be taken in the event of an accident
7. In accordance with the "Ethical Guidelines for Medical Research Involving Human Subjects," research ethics and the knowledge and skills necessary to conduct research

## 17 Committee for Regenerative Medicine, Hiroshima

### University

### 17.1 Deliberation by the Hiroshima University Committee for Regenerative Medicine

The Chairperson of the Hiroshima University Committee for Regenerative Medicine will deliberate on the progress report of clinical research once a year. The Chair of the Hiroshima University Committee for Regenerative Medicine may also deliberate at the request of the principal investigator or when he/she deems it necessary. The format of the deliberations will be decided by the chairperson according to the importance of the deliberations, such as convening a committee meeting, rotating the deliberations, or listening to opinions by telephone or e-mail.

## 17.2 Deliberations of the Committee for Regenerative Medicine, Hiroshima University

The Hiroshima University Committee for Regenerative Medicine will deliberate on the following matters.

1. Progress check
2. Whether or not to continue the research due to the occurrence of serious adverse events
3. Other matters deemed necessary by the chairperson

## 17.3 Recommendation by the Hiroshima University Committee for Regenerative Medicine

If a recommendation to be made is proposed, the content and reasons will be recommended to the principal investigator with the agreement of all deliberative committee members. In cases where the consensus of all committee members cannot be reached, the chairperson of the committee will summarize the opinions and make recommendations, including minority opinions.

(3) The administrator of the provider institution shall report to the committee on changes to the rehabilitation medical care provision plan and other measures taken after receiving opinions from the rehabilitation medical care commission.

# 18 Ethical Conduct of Clinical Research

This clinical research will be conducted with attention to the ethical principles based on the Declaration of Helsinki, and in compliance with the "Act on Securing the Safety of Regenerative Medicine, etc.", the "Ethical Guidelines for Medical Research Involving Human Subjects", and this protocol.

## 18.1 Committee for Regenerative Medicine, Hiroshima University

The Hiroshima University Committee for Regenerative Medicine, in consultation with the Hiroshima University Hospital administration, will deliberate on the implementation and continuation of clinical research from the perspective of ethical, scientific and medical validity, based on the contents of the clinical research protocol, explanatory documents (for patients and liver donors) and case report forms.

## 18.2 Progress report on clinical research

(2) With regard to the status of provision of regenerative medicine, etc., the following matters shall be reported to the Hiroshima University Regenerative Medicine Committee and the Minister of Health, Labour and Welfare.

(1) Number of persons who have received said regenerative medicine, etc.

(2) Occurrence and subsequent progress of the disease, etc. pertaining to the relevant regenerative medicine, etc.

(3) Evaluation of the safety and scientific validity of said regenerative medicine, etc.

(4) In cases where the provision of said regenerative medicine, etc. has been terminated, the date of termination.

This report shall be made every year starting from the date of submission of the plan for provision of regenerative medicine, etc. to the Minister of Health, Labour and Welfare, within 90 days after the expiration of said period. Reports to the Hiroshima University Committee for Biomedical Research and Innovation shall be made by submitting a report in accordance with Attachment Form 3, and reports to the Minister of Health, Labour and Welfare shall be made by submitting a report in accordance with Attachment Form 4.

## 18.3 Matters concerning the protection of human rights and personal information of subjects

### 18.3.1 Human rights of subjects

This research will be conducted in compliance with the "Declaration of Helsinki" by the World Medical Association, the "Act on Securing the Safety of Regenerative Medicine, etc.", and the "Ethical Guidelines for Medical Research Involving Human Subjects". From the perspective of protecting the human rights of subjects, the principal investigator and sub-investigators will carefully consider the appropriateness of requesting subjects to participate in this clinical research, giving due consideration to their health conditions, symptoms, age, gender, and capacity to consent. Particular care should be taken when subjects are socially vulnerable.

### 18.3.2 Protection of Personal Information

After obtaining the subject's consent, all handling of the case, including data management and manufacturing management, will be managed using a linkable anonymized subject identification code or registration number, and the comparison table of the anonymized code and the name and the consent form with the name will be kept strictly in a lockable document storage room. In addition, sufficient

consideration will be given to the protection of subjects' personal information, such as ensuring that the names of subjects are not directly disclosed in public announcements.

Personal Information Manager:.

Affiliation Graduate School of Medical Sciences, Hiroshima University Title  
[name] [name]

